**Methods:**

The FLUAM trial is a prospective, single-center, single-arm pilot trial to investigate the efficacy of 5-aminolevulinic acid-mediated photodynamic diagnosis (ALA-PDD)-assisted ULA for localized UTUC and the usefulness of the UroVysion® assay (multiprobe fluorescence in situ hybridization) as a monitoring test after the kidney-sparing treatment. After the screening and registration, a total of 20 patients with localized UTUC will undergo the initial ALA-PDD-assisted ULA followed by the second look ALA-PDD-assisted ureteroscopic examination. The primary endpoint is progression-free survival. Secondary endpoints include patient reported outcomes, diagnostic accuracy of UroVysion assay to detect tumor recurrence, adverse events, and safety of the intervention.

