The patients should be followed up closely in kidney-sparing management. Ureteroscopy with or without biopsy, cystoscopy, urinary cytology, and chest/abdominal/pelvic computed tomography (CT) or magnetic resonance imaging (MRI) are performed at regular intervals for surveillance [2,8]. Unfortunately, there is a significant lack of non-invasive reliable detection tools of urinary recurrent tumors in this treatment setting. Previous studies suggested that the UroVysion® test was a useful tool for the diagnosis not only of primary UTUC but recurrent UTUC after kidney-sparing surgery [17,18].

This prospective, single-center, single-arm pilot trial will investigate the efficacy and safety of ALA-PDD-assisted ULA for localized UTUC and the feasibility of UroVysion test combined with conventional urinary cytology as a detection marker of recurrent UTUC after the kidney-sparing surgery.

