### Protocol of Fluorescence In Situ Hybridization (FISH) assay

2.9

As exploratory research, we evaluate the diagnostic accuracy of UroVysion test of voiding urine specimens during follow-up and upper urinary tract irrigation or catheterized urine obtained by URS. Sample preparation is performed according to the protocol for UroVysion® FISH bladder cancer assay (SRL, Inc., Tokyo, Japan). We transfer urine sediments into ThinPrep® PresevCyt® Solution containing 55% methanol (UV7) and subject fixed samples to the SRL laboratory. Trained observers who are blinded for clinicopathologic data assess enumeration of FISH signals. This assay enables the visualization of molecular alterations, including aneuploidy of chromosomes 3 (red), 7 (green), and 17 (aqua) and loss of locus 9p21 (gold), which are frequently seen in human bladder cancer. Specimens are considered to be positive for UroVysion test if four cells or more have a gain of 2 or more chromosomes (3, 7, or 17) or 12 cells or more have a loss of both copies of locus 9p21 among observed 25 morphologically abnormal cells [18,22].

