### Statistical analysis

2.10

Descriptive statistics will be computed for all study variables. EZR 1.54 (Saitama Medical Center, Jichi Medical University, 2020) and PRISM software version 7.00 (GraphPad Software, Inc., San Diego, CA, USA) were used for statistical analyses and data plotting, respectively. A two-sided P value of less than 0.05 will be considered to be statistically significant.

The full analysis set population and the per protocol set population will be separately analyzed for both the primary endpoint (two-year PFS rate) and survival outcomes listed in the secondary endpoints (Fig. 1). The per-protocol set population will be analyzed for the other secondary endpoints. The PFS of study population will be estimated by Kaplan Meier method, and 95% confidence interval (CI) will be calculated using Greenwood's formula for variance. When the lower limit of 95%CI of two-year PFS rate is more than 58% (threshold survival rate), the ALA-PDD-ULA is considered superior to the conventional ULA without PDD assistance. When the lower limit of 95%CI of two-year PFS rate is 58% or less, the ALA-PDD-ULA is considered not superior to the conventional ULA without PDD assistance. In addition, a sensitivity analysis of the primary endpoint will be performed using the Fine-Gray subdistribution hazard regression. This model considers patients who die of other causes (competing events) before recurrence or progression.

The amount of change in other post-operative observations over time will be analyzed using the repeated measures analysis of variance, Wilcoxon signed-rank sum test, or Mann-Whitney *U* test as appropriate. Mixed-effects models for repeated measures will be applied to detect multiple change-points in longitudinal data. To evaluate the diagnostic accuracy of UroVysion test, the result is compared to the pathological diagnosis obtained by URS biopsy. The sensitivity, specificity, positive predictive value, negative predictive value, and diagnostic accuracy are determined according to standard methods [23]. The sensitivities of UroVysion test and the combination with the conventional cytology are compared to that of conventional cytology alone using McNemar's test.

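### UroVysion is compared with cytology on sensitivity alone, so the comparison cannot show whether a gain in sensitivity is bought with more false positives than cytology gives

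*Protocol article*

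**What the plan says.** All references are to the Protocol article.

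- **Reference standard** (2.10 Statistical analysis): "To evaluate the diagnostic accuracy of UroVysion test, the result is compared to the pathological diagnosis obtained by URS biopsy".
- **Measures estimated** (2.10): "The sensitivity, specificity, positive predictive value, negative predictive value, and diagnostic accuracy are determined according to standard methods". In context these describe UroVysion against biopsy.
- **Comparison with cytology** (2.10): "The sensitivities of UroVysion test and the combination with the conventional cytology are compared to that of conventional cytology alone using McNemar's test". No comparison of specificity, predictive value or accuracy with cytology is stated elsewhere in the article.
- **Significance level** (2.10): "A two-sided P value of less than 0.05 will be considered to be statistically significant".
- **Status**: section 2.9 opens with "As exploratory research, we evaluate the diagnostic accuracy of UroVysion test of voiding urine specimens during follow-up", while the Abstract says "Secondary endpoints include patient reported outcomes, diagnostic accuracy of UroVysion assay to detect tumor recurrence, adverse events, and safety of the intervention". The Abstract's Methods paragraph also makes the assay's usefulness for monitoring after kidney-sparing treatment one of the trial's two aims.

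The comparison sentence covers both UroVysion alone and UroVysion combined with cytology. The point here concerns UroVysion alone against cytology alone.

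**The concern.** Sensitivity by itself cannot rank two tests. A test that calls more specimens positive gains sensitivity whether or not it separates tumour from no tumour. What distinguishes a better test from a more liberal one is the behaviour of both tests in the same tumour-free patients, and the stated comparison leaves that out.

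This matters for a monitoring test. Section 2.6 schedules ten visits from month 1 to month 27, and at any given visit some patients will have no recurrence. Whether UroVysion raises more false alarms than cytology in those patients is part of whether it is useful. As the plan stands, the only P value set against cytology is unaffected by that question. UroVysion's specificity will be printed, but with no cytology figure from the same patients to read it against.

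**Working it through.** **There is no plan figure to reproduce.** The article gives no sample size, power, sensitivity or specificity for this comparison. The check has two parts: what the stated test can see, and an illustration under assumptions.

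**1. What McNemar's test on sensitivity uses.** Among n₊ biopsy-positive cases, let b be the number that are UroVysion-positive and cytology-negative, and c the reverse. The exact two-sided P value is min{1, 2·P[Bin(b+c, ½) ≤ min(b, c)]}, and the difference in sensitivity is (b − c)/n₊. Results in biopsy-negative cases appear nowhere in it. Among n₋ reference-negative cases, with b′ and c′ defined in the same way, the difference in specificity (UroVysion minus cytology) is (c′ − b′)/n₋. The article does not plan this second quantity.

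**2. Illustration.** Inputs:

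- Two-sided α = 0.05 (2.10) and 20 patients (2.7).
- Biopsy-positive patients, assumed range 6 to 18: the Introduction's 30.7% to 90.5% recurrence range applied to 20 patients (0.307 × 20 = 6.1; 0.905 × 20 = 18.1).
- Cytology sensitivity s, assumed 30% or 50%.
- An uninformative comparator, positive in a share u of specimens whatever the tumour status. Assumed u: 80%, 60% or 50%.
- One paired result per patient, and independent errors.

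The discordant-pair probabilities are P(b) = u(1 − s) and P(c) = (1 − u)s. The chance of a significant result in favour of the uninformative test is the sum of the trinomial probabilities over all (b, c) with b > c and exact P < 0.05.

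One case by hand: with n₊ = 6, only b = 6, c = 0 is significant (P = 2 × 0.5⁶ = 0.031; five against none gives 0.0625). With u = 0.8 and s = 0.3, P(b) = 0.8 × 0.7 = 0.56, so the probability is 0.56⁶ = 0.031.

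| Cytology sensitivity | Positive rate u | n₊ = 6 | 10 | 14 | 18 |
|---|---|---|---|---|---|
| 30% | 80% | 3% | 36% | 62% | 78% |
| 30% | 60% | 0.5% | 10% | 20% | 30% |
| 30% | 50% | 0.2% | 4% | 9% | 13% |
| 50% | 80% | 0.4% | 9% | 21% | 32% |
| 50% | 60% | 0.1% | 1% | 3% | 4% |
| 50% | 50% | <0.1% | 0.4% | 0.9% | 1.1% |

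**3. What joint reporting would show.** Take u = 80%, s = 30% and an assumed cytology specificity of 95%. The expected sensitivity difference is 80 − 30 = +50 points, and the expected specificity difference is 20 − 95 = −75 points. Side by side, these leave little room for misreading.

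**4. Why a second P value is not enough.** With cytology specificity 95% and UroVysion specificity 80% (both assumed), an exact McNemar test of specificity finds the loss in 0%, 0.4% and 2% of trials with 6, 10 and 14 tumour-free patients. At UroVysion specificity 70% the figures are 0.1%, 3% and 13%. A non-significant result would be usual even where the loss is real.

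**The case against.** The strongest case on the other side has five parts.

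- **False positives are already reported.** The plan commits to UroVysion's specificity, predictive values and accuracy against biopsy. A reader might infer that false positives go unreported, or that a worthless test could pass through the plan unnoticed. The documents do not support that: a test positive in 80% of specimens regardless of tumour would be published with a specificity near 20%. What remains is narrower, namely that no cytology specificity is set beside it.
- **No rule declares UroVysion better.** A reader might infer that a significant sensitivity result counts as superiority. The article defines superiority only for the two-year PFS rate. For UroVysion, a small P value says only that sensitivity is higher, which is true in the illustration. This stands.
- **Status.** The work is called exploratory in 2.9 and secondary in the Abstract, within a pilot trial. The Introduction speaks of "the feasibility of UroVysion test combined with conventional urinary cytology as a detection marker of recurrent UTUC after the kidney-sparing surgery", which concerns the combination and not UroVysion alone. This limits the weight of the point.
- **The high percentages come from an extreme choice.** Nothing in the documents supports 80% positivity irrespective of tumour, and 2.9 fixes the cut-off and blinds the readers. If photodynamic assistance lowers recurrence as the trial hopes, the number of biopsy-positive patients moves towards the low end, where the figures are 3% or less. This stands, and the percentages are illustrative only.
- **A condensed article may leave further tables to the full protocol or analysis plan.** This stands only in part. The article does not merely stay silent: it states the comparison, its measure and its test, and covers one side of accuracy.

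**Conclusion.** The point holds as a minor weakness in a stated analysis choice. The only stated comparison with cytology is confined to biopsy-positive cases, so it cannot show whether higher sensitivity comes with more false positives than cytology gives. That follows from the structure of the test and needs no assumption. It limits what can be concluded about UroVysion relative to cytology as a monitoring test. It does not make the sensitivity comparison wrong, and it does not touch the primary endpoint.

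How often a misleading impression could arise is not known from the documents. Against an assumed cytology sensitivity of 30%, with 6 to 18 biopsy-positive patients, the range is 3% to 78% at 80% positivity and 0.2% to 13% at 50% positivity. It is lower still if cytology sensitivity is 50%. All of this rests on independent errors and one pair of results per patient.

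**What to change.** In section 2.10, beside the existing McNemar sentence:

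1. Tabulate cytology's specificity in the same reference-negative patients or specimens as UroVysion's. The second-look ureteroscopy, planned for all patients, is a natural source. If tumour-free patients are not biopsied there, say what counts as reference-negative; the specificity already planned for UroVysion needs that definition too.
2. Report the paired UroVysion-minus-cytology differences in sensitivity and in specificity side by side, each with an exact 95% confidence interval.
3. State that any conclusion on UroVysion versus cytology will rest on both estimates rather than on the sensitivity P value alone, and that a non-significant specificity difference will not be read as no loss.

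UroVysion need not be better on both measures. A trade-off may be acceptable, provided both sides of it are shown.

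The cost is one more 2×2 table, from tests that already appear in the schedule, and a few lines of text. The downside is a wide interval for the specificity difference with so few patients, and a possibly less favourable statement on UroVysion.

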### Dissemination

2.11

The results will be submitted to peer-reviewed journals for publication and presented at local and international scientific conferences. Also, the results will be made available to interested participants.

## Conclusion

3

The goal of this trial is to determine the potential benefit of ALA-PDD assistance in patients who undergo the ULA. The evidence of this novel technique is still limited. The results are expected to change the standard of care and lead to better management of localized UTUC.

## Trial status

The study began in July 2021. Patient recruitment has not yet been completed, and the intervention program is ongoing. A follow-up and data collection will be completed in June 2026. The final results are expected in September 2026.

## Ethics approval and consent to participate

This clinical trial complied with the Declaration of Helsinki regarding investigation in humans. Its ethical clearance and protocol (version 1.0 on June 21st, 2021) including the subject information, informed consent forms, and associated documents, were approved by the Certified Review Board of Nara Medical University (institution ID: CRB5200002). Informed consent and written consent forms of patients are mandatory before study participation. This clinical trial was prospectively registered with the Japan Registry of Clinical Trials on June 28th, 2021 (the reference number: jRCTs051210042).

## Consent for publication

Not required.

## Availability of data and materials

The collected datasets used during this clinical trial are available from the corresponding author ([name]) on reasonable request.

